### Study setting and recruitment

To account for anticipated dropout and screen failure rate, the PAINLESS study will enrol approximately 49 participants in the screening period to achieve a randomised sample size of 40 participants in total across two research sites in the United Kingdom – Sheffield Teaching Hospitals National Health Service (NHS) Foundation Trust and University Hospitals of Leicester NHS Trust. The study recruited its first participant on 27^th^ March 2026. Recruitment is ongoing with a planned recruitment period of 12 months, estimated to complete enrolment by 9th February 2027. Participants will be recruited from specialist PDN clinics, and their aligned primary care and podiatry services. Recruitment will be supported through digital promotion, including social media, and via local patient groups and charities. All study investigations and interventions will take place in clinical research facilities at the two sites. Data collection is expected to complete by September 2027 with results expected to be shared by February 2028.

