#### Sample size justification.

To detect a minimally important difference of 0.75 NRS points (between-patient SD of 2, within-participant SD = 1.44) with 90% power and two-sided α = 0.05, a crossover/pairwise comparison requires 39 evaluable participants. Allowing for 20% dropout during the eligibility screening period, we will recruit up to 49 participants. The 0.75-point NRS difference reflects a 15% reduction from a conservative baseline NRS of 5, consistent with IMMPACT guidelines which define a 15% between-group difference as clinically meaningful [18]. Calculations use the within-individual SD appropriate for crossover designs and therefore are conservative for detecting a true within-participant treatment effect. Using a lower baseline than typically seen in NeuP trials ensures the study is robustly powered, even in patients with milder pain (effect size 0.52). Our estimated dropout rates are conservative and allow for an increased dropout rate compared to previous HCL trials [14,16].

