## Discussion

The crossover design of this study allows for within-participant comparisons, reducing confounding and maximising data collection. By allowing each participant to serve as their own control, the study increases statistical power while ensuring ethical access to the HCL treatment for all study participants. Furthermore, the planned withdrawal of HCL in half of participants provides an opportunity to evaluate whether neuropathic pain returns to baseline levels following the intervention period.

Despite these strengths, certain limitations are inherent to the study design. Due to the interactive nature of HCL, blinding participants to their treatment sequence is not feasible. There is also a risk of attrition bias, as the order of treatment may influence retention. For example, participants randomised to the intervention first might be more prone to dropping out before the crossover phase.

TIND is a phenomenon in which rapid improvements in glycaemia can cause or accentuate painful diabetic neuropathy [38]. HCL has been demonstrated to achieve improvement in glycaemia [15], and a potential pitfall of the design is that a rapid improvement in glycaemia following HCL start might transiently worsen pain outcomes in some participants. To mitigate this risk, the protocol incorporates a two-week open loop period for participants with a high baseline HbA1c to ensure a more gradual transition. However, TIND could potentially act as a confounder or diluter of the primary outcome results.

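### The only dropout allowance (20%) is spent on screening, so 40 randomised leaves room to lose one participant before the 39 evaluable needed for 90% power is missed

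*Protocol article*

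**What the plan says.** All statements are in the protocol article.

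- **Sample size justification, target.** "To detect a minimally important difference of 0.75 NRS points", with a "between-patient SD of 2, within-participant SD = 1.44", the section states that "with 90% power and two-sided α = 0.05, a crossover/pairwise comparison requires 39 evaluable participants".
- **Sample size justification, allowance.** "Allowing for 20% dropout during the eligibility screening period, we will recruit up to 49 participants". No other loss rate appears in the section. It then adds: "Our estimated dropout rates are conservative and allow for an increased dropout rate compared to previous HCL trials".
- **Study setting and recruitment.** To cover both dropout and screen failure, the trial will enrol "approximately 49 participants in the screening period to achieve a randomised sample size of 40 participants in total".
- **Abstract.** It gives 49 adults as the number recruited and describes each participant as completing both periods. It does not separate those screened from those randomised.
- **Participant timeline and data collection.** It provides for participants who stop the intervention, stop follow-up or stop data collection.
- **Statistical analysis.** An endpoint counts as missing when fewer than five of the last seven daily scores are present. Missing scores are multiply imputed, and all randomised participants are analysed.
- **Discussion.** Attrition bias is named as a risk, with the example that "participants randomised to the intervention first might be more prone to dropping out before the crossover phase".

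**The concern.** In a crossover trial, the precision of the treatment contrast comes mainly from participants who supply the endpoint in both periods. The figure of 39 is a requirement for evaluable participants, so any inflation should cover everything that happens between enrolment and the second endpoint. Here the sample size section ties its one allowance to the screening phase, and the recruitment section confirms this by giving 40 as the number randomised. Nothing is left for 24 weeks of treatment.

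Two statements suggest otherwise. The recruitment section says the 49 covers dropout as well as screen failure. The sample size section presents its dropout rates as a margin over earlier HCL trials. A reader would conclude that in-trial dropout has been generously provided for, when the only rate given applies before treatment starts. At stake is whether the stated 90% power describes the trial as it is planned to run.

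**Working it through.** **Inputs** (Sample size justification unless noted): difference δ = 0.75; SD = 1.44; two-sided α = 0.05, so z = 1.960; power 90%, so z = 1.282; 39 evaluable; 20% allowance; 49 recruited; 40 randomised (Study setting and recruitment). The post-randomisation loss rate is not given. I assume 5 to 20%.

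**Step 1: reproduce 39.** Normal approximation for a paired comparison:

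n = [SD × (1.960 + 1.282) / δ]² = [1.44 × 3.242 / 0.75]² = 38.7, rounded up to 39.

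This uses 1.44 as the SD of the paired difference, which agrees with the section's effect size of 0.52 (0.75/1.44 = 0.521).

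**Step 2: reproduce 49.** 39 / (1 − 0.20) = 48.75, rounded up to 49. The whole 20% goes into this step.

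**Step 3: what is left after randomisation.** From 49 enrolled to 40 randomised is a loss of 9/49 = 18.4%. From 40 randomised to 39 evaluable is a loss of 1/40 = 2.5%.

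**Step 4: power at the number of complete pairs n.** By the article's formula, power = Φ(δ√n/1.44 − 1.960). For n = 36: 0.75 × 6/1.44 = 3.125; 3.125 − 1.960 = 1.165; Φ = 87.8%. The paired t-test (noncentral t, n − 1 degrees of freedom) is a check.

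| Loss after randomisation (assumed) | Complete pairs of 40 | Power, article's formula | Power, paired t |
|---|---|---|---|
| 0% | 40 | 90.9% | 89.5% |
| 2.5% | 39 | 90.2% | 88.7% |
| 5% | 38 | 89.4% | 87.8% |
| 10% | 36 | 87.8% | 86.0% |
| 15% | 34 | 85.9% | 83.8% |
| 20% | 32 | 83.8% | 81.4% |

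The two columns should not be mixed. The t-test is just under 90% even with no loss, so a drop attributed to attrition must be read down one column.

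**Step 5: chance of reaching 39.** If participants are lost independently, the probability of keeping at least 39 of 40 is 40% at 5% loss, 8% at 10%, 1.2% at 15% and 0.15% at 20%.

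**Step 6: what holding 39 would take.** 39/(1 − loss), rounded up, gives 42, 44, 46 or 49 randomised at 5, 10, 15 or 20% loss. With the 20% screening loss on top, that is 53, 55, 58 or 62 entering screening.

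**The case against.** The strongest reply is that the shortfall is small. By the method that produces 39, a 5% loss costs 0.6 points against 90%, and a 20% loss still leaves power above 80%. That stands. A reader might infer that 90% power collapses under any realistic loss, but the figures do not support this.

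Second, dropping out of treatment is not the same as losing an endpoint. Consenting participants who stop the intervention stay on the assessment schedule, the endpoint is a diary needing five of seven days, and randomisation requires 70% diary and CGM completion over the screening period. This also stands: the table counts lost endpoints, so equating every dropout with a lost pair would be a worst case.

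Third, multiple imputation keeps all randomised participants in the analysis. That is true, but it does not restore the within-participant contrast for someone whose second endpoint is missing.

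Other stronger readings fail:

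- **40 as an arithmetic error.** 49 × 0.8 = 39.2, but the recruitment section says approximately, so this is rounding.
- **Far lower power from reading 1.44 as a per-period SD.** That is a separate question about the SD and is not caused by attrition.
- **Dropout as an expectation of the Discussion.** It describes a risk, with an example.
- **The permitted three-month delay as exposure after randomisation.** The article places it between baseline and the HCL start, without saying whether randomisation comes first.
- **The conservative claim as disproved.** The cited HCL trials are not at hand, so their dropout cannot be compared. What can be said is that the only stated rate concerns screening.

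**Conclusion.** The point holds as a modest misstatement that should be fixed. The plan's 90% power requires 39 evaluable participants, its only stated allowance is consumed before randomisation, and 40 randomised tolerates one loss. The recruitment section's description of what the 49 covers, and the claim that the dropout rates are conservative, are not borne out by the article's own numbers.

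By the article's formula, expected power is about 88% at 10% loss of complete pairs and about 86% at 15%. This rests on 1.44 being the SD of the paired difference, on assumed loss rates, and on counting only participants with both endpoints as informative. The trial remains reasonably powered across the assumed range. What needs correcting is the stated property.

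**What to change.** 1. In the sample size section, give two separate rates: loss during screening, and loss of a primary endpoint in either period after randomisation.
2. Keep 40 randomised and restate power at the expected number of complete pairs, for example about 88% at 10% loss (36 pairs) or 86% at 15% (34 pairs) by the article's formula.
3. Remove the claim that the dropout allowance is conservative relative to HCL trials, or limit it to screening.
4. Align the Abstract, Study setting and recruitment, and Sample size justification on the numbers screened (49), randomised (40) and expected to be evaluable.

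The cost is wording and a slightly less favourable stated power. No extra enrolment is needed to make the statement correct. Holding 39 evaluable would need the larger numbers in Step 6, which is a separate decision for the sponsor.

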#### Data management.

Sheffield Teaching Hospitals NHS Foundation Trust has policies in place which are designed to protect the security, accuracy, integrity and confidentiality of Personal Data. The trial will be registered with the Data Protection Officer and will hold data in accordance with the Data Protection Act (2018 and subsequent amendments). Personal details for each participant taking part in the study will be linked to a unique identification number held locally on a study screening log in the investigator site file at each site. All participant-related reports and communication transferred to the sponsor will be identified by this identification number only. User accounts for Dexcom clarity, Glooko and Tandem Connect will be pseudonymised, using the study identification number and a fake date of birth. Database lock will take place once all data entries have been checked and sufficient verification processes are completed.

#### Reducing bias and ensuring objective assessment.

Although participants and clinicians cannot be blinded to HCL use, we will minimise bias through several measures. Pain and sleep diaries collected from intervention visits will be analysed by an assessor blinded to treatment allocation. Analyses will be conducted by a statistician blinded to treatment sequence (the treatment sequence will be coded). Outcomes include objective metrics (CGM, activity logs) alongside standardised daily pain and sleep diaries. A pre-specified analysis plan and crossover design further reduce bias, with each participant serving as their own control. Independent oversight will monitor data quality and interpretation.

#### Statistical analysis.

The primary analysis will be conducted using an intention-to-treat (ITT) approach, including all participants who were randomized. As a preliminary step prior to the primary analysis, the change in the coefficient of variation (CV) between the control intervention period and HCL intervention period will be evaluated to assess intervention effect on glycaemic variability. The primary analysis will proceed regardless of whether a statistically significant difference in glucose CV is observed. A linear mixed-effects model will be used to assess the primary outcome, with all analysis performed by a statistician blinded to the allocation of treatment sequences. The model will include treatment arm, period, sequence, gender at birth, centre and age group as fixed effects and participant as a random effect to account for the repeated measures design. Model assumptions will be assessed using residual versus fitted plots and Q-Q plots of residuals. The NRS pain score (0–10) will be analysed as a continuous outcome, consistent with established practice in chronic pain trials. If model assumptions are violated, sensitivity analyses using alternative modelling approaches will be considered. The primary hypothesis will be tested at a two-sided significance level of α = 0.05. To minimise the risk of bias associated with missing data, a multiple imputation approach will be used as the primary method for handling missing NRS scores. This analysis will include all randomised participants. A participant’s NRS score will be considered missing if fewer than five daily pain scores are recorded in the final seven days of the treatment period. Sensitivity analyses will be conducted, including a per-protocol analysis, to evaluate the robustness of the primary findings. Secondary outcomes will be analysed, comparing changes from baseline to the end of the treatment period, between the two treatment arms. Exploratory analyses will examine the impact of the HCL system on objective neurophysiological assessments (Sudoscan, DPN-Check, Vibrosense and Vagus) by correlating changes in glycaemic metrics with changes in neurophysiological data; and examine how change in a participant’s NRS score correlate with physical activity and sleep parameters.

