## Introduction

Diabetic peripheral neuropathy (DPN) is the most common complication of diabetes [1]. Although DPN can be asymptomatic, up to one-third have painful diabetic neuropathy (PDN) [2]. This is a disabling condition with a profound impact on quality of life, sleep, and mental health [3]. Current pharmacotherapy offers limited efficacy and tolerability [4] with only 54% of patients achieving 50% pain relief on maximal combination therapy [5]. Options for ‘refractory’ neuropathic pain (NeuP) are limited. Opioids carry significant risks and offer no long-term benefit [6], while spinal cord neuromodulation is invasive, costly and unsuitable for many [7]. Other interventions lack robust evidence or availability [4], leaving a major unmet clinical need.

Glycaemic variability (GV), reflecting fluctuations in glucose independent of overall glycaemic exposure, has been linked to fluctuations in pain intensity and has been identified as a potential modifiable therapeutic target [8]. Putative biological mechanisms to suggest the link between glycaemic variability and pathogenesis of diabetic neuropathy have been proposed, primarily via the induction of oxidative stress and systemic inflammatory responses [9]. Specifically, GV has been demonstrated to trigger the NF-kB and PKC pathways, leading to cellular damage that manifests as neuropathy. Continuous glucose monitoring (CGM) now allows precise measurement of GV, including coefficient variation (CV) and standard deviation of glucose (SD) [10]. A meta-analysis of 3,649 people with type 1 diabetes (pwT1D) and type 2 diabetes (T2D) demonstrated a two- to three-fold increased risk of DPN in those with higher GV [11]. Furthermore, GV has been specifically implicated in the development of painful over painless diabetic neuropathy [8,12]. Lower time in range (TIR), was significantly associated with an elevated risk and severity of PDN, independent of other risk factors [8]. However, whether reducing GV can directly modify pain intensity in PDN remains unknown.

Hybrid closed loop (HCL) insulin delivery systems automate basal insulin dosing using CGM data and predictive algorithms [13]. Randomised controlled trials consistently show that HCL improves overall glycaemic control and reduces GV [14–17]. This raises the possibility that HCL could modify pain intensity in PDN by stabilising glucose fluctuations.

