#### HCL intervention period: HCL + CGM (t:slim X2 + Dexcom G7).

At the start of the HCL intervention period, participants will attend an in-person training visit for instruction of use of the Control-IQ and a Dexcom G7 CGM, based on manufacturer guidelines. The t:slim X2 is a tethered insulin pump licensed in the UK for use with quick acting insulins (Humalog, NovoRapid, Lyumjev, Admelog, and Trurapi) [23]. Control-IQ is an advanced HCL algorithm that uses predictive technology to automatically modulate insulin delivery. It reduces or suspends basal insulin to mitigate impending hypoglycaemia and increases basal insulin delivery and administers automated correction boluses to address impending hyperglycaemia. The system also includes temporary modes for sleep and exercise that adjust glycaemic targets, and allows for the creation of multiple insulin profiles to accommodate different situations, such as illness. Comprehensive education will be provided on sick-day management, including protocols for preventing diabetic ketoacidosis and instructions to switch to back-up insulin pens in the event of pump malfunction or infusion set failure.

The 12-week data collection period will commence after the training visit. All devices will be connected to the Tandem t:slim X2 mobile app to facilitate continuous cloud-based data upload. To ensure a safe transition to the new technology, a dedicated safety visit (Visit 3A) will be arranged shortly after the first scheduled infusion set change. At subsequent clinical visits, a diabetes clinician will review pump and CGM data, and provide advice to optimise pump settings. Concordance with hybrid closed loop treatment will be reviewed. The key therapeutic focus will be on improving glycaemic variability. To mitigate the risk of treatment-induced neuropathy of diabetes (TIND), a gradual reduction in average glucose levels will be implemented for participants with higher baseline HbA1c (>11.0%), by use of the pump in open loop mode for up to two weeks. A dedicated support number will be available for participants in all arms and sequences of the study. If ongoing treatment with HCL was deemed to be deleterious by the principal investigators, for example, due to worsening neuropathic pain, recurrent diabetic ketoacidosis, or any unforeseen recurrent or persistent issue, the trial participant would be returned to standard care.

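### Comparing glucose CV between HCL and control before the primary analysis is likely to reveal the treatment code to the statistician described as blinded

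*Protocol article*

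**What the plan says.** Four statements in the protocol article bear on this.

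- **Order.** Statistical analysis: "As a preliminary step prior to the primary analysis, the change in the coefficient of variation (CV) between the control intervention period and HCL" periods is examined. The stated purpose is that it "will be evaluated to assess intervention effect on glycaemic variability".
- **Role of the result.** The next sentence says: "The primary analysis will proceed regardless of whether a statistically significant difference in glucose CV is observed". The CV comparison is not a gate.
- **Who analyses.** The primary model is described "with all analysis performed by a statistician blinded to the allocation of treatment sequences". The section on reducing bias says: "Analyses will be conducted by a statistician blinded to treatment sequence (the treatment sequence will be coded").
- **Expected direction.** The Introduction states: "Randomised controlled trials consistently show that HCL improves overall glycaemic control and reduces GV". The description of the HCL period adds: "The key therapeutic focus will be on improving glycaemic variability".

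The article does not say who runs the CV comparison, whether it uses coded labels, or that the code is opened for it.

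**The concern.** Participants and clinicians know the treatment, and the primary outcome is self-reported pain. Blinding the analyst is one of several safeguards the protocol claims, alongside a blinded diary assessor, objective measures, a pre-specified plan, the crossover design and independent oversight. It is the safeguard that the order of analysis affects.

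A contrast between HCL and control periods needs either the true labels or coded ones. If coded, its direction carries information, because the protocol says in advance which treatment should have the lower variability. The Randomisation section has only two sequences, so identifying one code decodes every participant. The pain result would not give the code away in the same way, since the Introduction treats the effect of lower variability on pain as unknown.

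What is at stake is whether the choices that remain after the CV step can truthfully be reported as made blind. These are the detail of the imputation model, the judgement on residual and Q-Q plots, the choice of sensitivity models, and per-protocol membership.

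**Working it through.** **Inputs from the documents.** Sample size justification: difference 0.75 NRS points, SD 1.44, 90% power, two-sided alpha 0.05, 39 evaluable, 49 recruited. The Study setting section gives 40 randomised.

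**The plan's own figure.** Taking 1.44 as the SD of the paired difference:

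n = (1.960 + 1.282)² × (1.44 / 0.75)² = 38.73, rounded up to 39. Then 39 / (1 − 0.20) = 48.75, rounded up to 49.

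Both figures reproduce, and 39 pairs are used below.

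**Inputs that must be assumed.** The documents give neither an expected CV reduction nor an SD for the within-participant CV difference. I take a true fall of 0.5 to 3 percentage points and an SD of differences of 4 to 8 points.

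**Formula.** If the analyst takes the code with the lower mean CV to be HCL, the probability of being right is Φ(δ × √n / SD), where δ is the true fall. A guess without data is right with probability 0.5.

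**Worked cases, n = 39.**

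- δ = 1, SD = 6: standard error 6 / √39 = 0.961; z = 1 / 0.961 = 1.04; probability 0.85.
- δ = 2, SD = 8: standard error 8 / √39 = 1.281; z = 2 / 1.281 = 1.56; probability 0.94.

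| True fall in CV (points) | SD 4 | SD 6 | SD 8 |
|---|---|---|---|
| 0.5 | 0.78 | 0.70 | 0.65 |
| 1 | 0.94 | 0.85 | 0.78 |
| 2 | 0.999 | 0.98 | 0.94 |
| 3 | >0.999 | 0.999 | 0.99 |

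With the 40 randomised, δ = 1 and SD = 5 give z = 1.26 and probability 0.90, so 39 or 40 makes no practical difference.

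In standardised terms (fall divided by SD of differences), effects of 0.1, 0.2, 0.3 and 0.4 give 0.73, 0.89, 0.97 and 0.99.

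**What this measures.** It is the chance of identifying the label from the sign alone. It is not a bias in the NRS difference, a type I error or a loss of power, and the documents offer no basis for computing any of those.

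**The case against.** The strongest case on the other side has four parts.

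1. **A reader might infer that the plan breaks the code.** The documents do not support that. The sequence is coded, no section opens the code, a CV contrast can be run on coded labels, and the CV sentence names no analyst. The phrase about all analysis is attached to the primary model and could be read as covering that model only. This stands as a limit on certainty. However, the section on reducing bias states the blinding for analyses in general, and nothing exempts the CV step.

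2. **A reader might infer that an unmasked analyst could swap the primary model.** The text rules this out: "If model assumptions are violated, sensitivity analyses using alternative modelling approaches will be considered". The per-protocol analysis is also listed as a sensitivity analysis. The randomised population, mixed model, fixed effects, random effect, alpha, use of multiple imputation and rule of fewer than five of seven daily scores are all stated. This stands, and it is why the possible bias is limited.

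3. **Imputation detail and the per-protocol definition may be settled in an analysis plan that is not shown.** That is possible, and it would narrow the exposed choices further. It would not restore the blind if that plan keeps the order stated here.

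4. **The main exposure in an open-label pain trial is participant reporting, which analysis order does not affect.** This is true, but it does not justify claiming a safeguard that the stated order weakens.

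**Conclusion.** The stated order and the stated blinding do not sit well together. Running the CV comparison first is likely to reveal which code is HCL before the primary NRS analysis. Over the assumed range the probability is 0.94 or more for a true fall of at least 2 points, and 0.65 to 0.94 for falls of 0.5 to 1 point. It depends on assumed values, and on the CV step being done by, or reported to, the statistician who runs the primary model.

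The consequence is modest. The CV result has no stated route into the primary test, and most of the primary analysis is fixed beforehand. What may not be blind in practice is imputation detail, the judgement on model assumptions, the choice of sensitivity models and per-protocol membership. No sample size or error rate changes. The point is worth correcting because the safeguard is claimed and the correction is cheap.

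**What to change.** In the Statistical analysis section, delete the opening words that place the CV comparison ahead of the primary analysis. State instead that CV and the other CGM-derived outcomes are compared after the primary NRS analysis, the imputation and the per-protocol set have been finalised under coded labels. Nothing inferential is lost, because the primary analysis goes ahead whatever the CV result. If the team prefers to keep CV first, a separate statistician could run it and withhold the result until that point.

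The cost is small but not zero. CGM-derived variables must be kept out of the blinded analysis dataset until the primary analysis is final, which means a staged release of data. If CGM or pump-use data are intended for the imputation model or for per-protocol membership, the plan should say how they are supplied without showing the arm. The target of 39 evaluable, the recruitment of 49 and alpha of 0.05 are unchanged.

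### The effect of HCL on the neurophysiological tests is to be examined by correlating change scores, which does not estimate that effect, although the randomised contrast is available

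*Protocol article*

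**What the plan says.** The Statistical analysis section of the protocol article states the question as follows: "Exploratory analyses will examine the impact of the HCL system on objective neurophysiological assessments". The same sentence then gives the method: "correlating changes in glycaemic metrics with changes in neurophysiological data". It names no HCL-versus-control comparison for these tests. The other exploratory analysis listed there is to "examine how change in a participant’s NRS score correlate with physical activity and sleep parameters".

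The preceding sentence does give a randomised comparison, but for a different class of outcome: "Secondary outcomes will be analysed, comparing changes from baseline to the end of the treatment period, between the two treatment arms".

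The article is not consistent about where the neurophysiological tests belong:

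- The Abstract and the Exploratory endpoints section call them exploratory.
- Table 2, the list of pre-specified secondary outcomes, does not contain them.
- The Blinding (masking) section counts them among the secondary outcome assessments.

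Nor is it consistent about what they are for. The Exploratory endpoints section presents them as a way to study mechanisms and how variability in glucose acts on nerve measures. The Statistical analysis section presents them as a way to study what HCL does.

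**The concern.** The effect of HCL on a nerve measure is a contrast between the two randomised conditions. A correlation between glycaemic change and nerve-test change answers another question: do participants whose glucose changed more also show more change in the test? How much a participant's glucose changes is not randomised. It depends on adherence, starting control, illness and, in the control period, on the clinician's advice about insulin. Any of these may also influence the nerve test.

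Two errors could follow. A real effect of HCL on nerve function could go unseen because it was much the same in everyone. Or an association with another cause could be reported under the label of an HCL effect. In either case, the evidence that randomisation provides would be left out of the stated analysis.

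**Working it through.** **1. Is the randomised contrast available?** Yes. The Neurophysiological tests section schedules all four assessments at baseline and again at the close of each period. Each completer therefore supplies a result under HCL and one under control. The primary model in the Statistical analysis section already has treatment, period and sequence as fixed effects and participant as a random effect, and can be applied to these measures as it stands.

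**2. What does the correlation measure?** For one participant, let D_y be the HCL-minus-control difference in a nerve measure and D_g the same difference in a glycaemic metric. Leaving period effects aside:

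- D_y = τ_y + e_y
- D_g = τ_g + e_g

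Here τ_y and τ_g are the mean effects of HCL, and e_y and e_g are individual deviations with mean zero. Then:

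- Treatment effect on the nerve measure: mean of D_y = τ_y
- Correlation of the differences: cov(e_y, e_g) / [SD(e_y) × SD(e_g)]

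The correlation does not contain τ_y. The same holds if changes from baseline are correlated within one condition. If changes from both conditions were put in one correlation, the covariance would gain a term τ_g × τ_y / 4 from the gap between the arms. That term would be mixed with the non-randomised part and could not be read as the effect of HCL. The article does not say which form is meant; none of them estimates τ_y.

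**3. Number of participants for an illustration.** The Sample size justification gives 39 evaluable, which reproduces with 1.44 as the SD of the within-participant difference:

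- n = (1.44 × (1.9600 + 1.2815) / 0.75)² = 38.73, so 39
- 39 / (1 − 0.20) = 48.75, so 49 recruited
- standardised effect: 0.75 / 1.44 = 0.52

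**4. Illustration at n = 39.** The documents give no SDs or effects for the nerve tests, so the values below are assumptions. Differences are scaled to SD 1, and HCL moves the glycaemic metric by 1 SD. The shift of 0.52 SD is borrowed from the pain calculation only to fix a scale. There were 20,000 simulated trials per row, with two-sided tests at 5%.

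| Assumed truth | Mean r | Correlation significant | Paired HCL-minus-control contrast significant |
|---|---|---|---|
| HCL shifts the nerve measure by 0.52 SD in everyone; no individual link with glucose | 0.00 | 5.1% | 88.9% |
| HCL has no effect on the nerve measure; a shared cause gives r = 0.5 | 0.50 | 91.8% | 4.9% |

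Closed forms agree. Paired t power at 39 for an effect of 0.75 / 1.44 is 88.7%. By Fisher's z, power for r = 0.5 is Φ(0.549 × √36 − 1.96) = Φ(1.34), about 91%.

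**5. How informative is the correlation as an association?** At n = 39, power for r = 0.3 is Φ(0.3095 × 6 − 1.96) = Φ(−0.10), about 46%. An r of about 0.44 is needed for 80% power. A null correlation would therefore say little.

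**The case against.** The strongest reply has three parts.

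*The between-arm comparison may already be intended.* The Blinding (masking) section calls these tests secondary, and secondary outcomes are compared between arms. This shows that their status is unsettled, but it does not remove the problem. Table 2 leaves them out, two other places call them exploratory, and the only sentence in the Statistical analysis section that names the four devices prescribes correlation. It is fair to add that the article does not exclude a randomised comparison; it only fails to state one for these tests.

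*Correlation fits the purpose.* For the aim in the Exploratory endpoints section, how glucose variability relates to nerve measures, a correlation is a reasonable exploratory tool. This stands. The fault lies in using it for a question worded as the effect of HCL.

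*These are exploratory endpoints.* This also stands, and it limits the weight of the point.

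Two stronger readings are tempting and should not be drawn:

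- A reader might infer that two change scores per participant will be pooled as if independent, which would inflate the type I error. The article says nothing about rows per participant or the test to be used, and its wording fits one difference per person equally well.
- A reader might infer that the trial omits its own motivating question, since the Introduction says that "whether reducing GV can directly modify pain intensity in PDN remains unknown" and no listed analysis relates change in glucose variability to change in pain. The article does list the effect of HCL on glucose CV, which "will be evaluated to assess intervention effect on glycaemic variability", and the effect of HCL on pain as the primary analysis. It also refers to a pre-specified analysis plan, which is not shown and could well contain the individual-level association.

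**Conclusion.** The point holds as a mismatch between question and method in the text itself: the Statistical analysis section assigns to the question of HCL's effect on the nerve tests a method that cannot estimate it. The algebra needs no assumption about the size of any effect. The simulated percentages do rest on assumed standardised effects and a shared-cause correlation of 0.5. They show the direction and possible scale of the error and are not forecasts for this trial.

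Severity is minor. The primary pain comparison, its error rate and the sample size are unaffected. What is at risk is the interpretation of the neurophysiological results.

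**What to change.** 1. For each continuous neurophysiological measure, estimate HCL minus control with the primary mixed model (treatment, period, sequence and the other stated covariates as fixed effects, participant as random effect), and report it with a confidence interval as exploratory.
2. Keep the correlation with glycaemic metrics, but run it on one HCL-minus-control difference per participant, adjusted for sequence so that period effects drop out, and call it an association.
3. Align the Exploratory endpoints, Blinding (masking) and Statistical analysis sections: give these tests one status, and state the HCL effect and the glucose association as two separate aims.

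The cost is a few sentences and a little more analysis on data that the schedule already collects. Recruitment is still under way, so it can be settled before database lock.
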